### Intervention

In 2019, the “NingBX neonatal homogeneity platform” team developed a WeChat mini-programs named “Ning BX breastfeeding”, which is used to address the problems related to breastfeeding and lactation consultation of premature infants and mothers with NICU mother-infant separation. The “Ning BX breastfeeding” WeChat mini-programs have been in the trial phase at Nanjing Maternity and Child Health Care Hospital, with very promising results. The “Ning BX breastfeeding” WeChat mini-programs are divided into the doctor version and guardian version. By scanning the corresponding QR code, a mobile number can be entered and used to register and log in. A mobile number can be registered only once to protect the privacy of users and prevent information leakage. The WeChat mini-programs educators will be responsible for obtaining informed consent from the guardians of premature infants. Informed consent was provided by the guardians of all participants, who could be withdrawn at any time according to the wishes of their guardians without affecting any treatment. By binding the corresponding hospital and designating the doctor, information can be shared. The “Ning BX breastfeeding” WeChat mini-programs is divided into four parts (Fig. 3): Mother’s Daily, Baby Feeding, Growth Record, and Growth Curve.

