### Eligibility and exclusion criteria

#### Inclusion criteria

Preterm infants weighing less than 2000 g and/or with a gestational age of less than 34 weeks.The guardians of all preterm infants will provide informed consent.

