#### Exclusion criteria

Pregnancy with serious diseases (such as malignant tumour, epilepsy or heart dysfunction), infectious diseases, or other medical contraindications for breastfeeding (such as galactosemia);No parental consent.

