### Randomization

Because the intervention cannot be completely blinded in this study due to the randomization of groups as units and differences in NICU scale, a whole-group matching design will be adopted. Twelve units will be randomized into two groups (intervention and control groups) instead of patient randomization to avoid the confounding effect of patients in the control groups. Two NICUs with a similar number of premature infants, the same NICU scale, and approximately the same range of MOM feeding taken as a floor will be randomly divided into six groups. Next, the names of 12 units will be written on paper and placed in the same envelope. One third-party individual blinded to this project will take one envelope from each of the six groups, and the six chosen envelopes will be assigned to the intervention group. The remaining six envelopes will be assigned to the control group.

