### Pre intervention training

Before the study, the supervision unit will be responsible for the training on the use of the “Ning BX breastfeeding” WeChat mini-programs and the development of a user guide. The intervention group unit will establish a “Ning BX breastfeeding” WeChat mini-programs implementation team comprising at least one neonatologist and one neonatal nurse. Each participant needs to be trained in the use of the “Ning BX breastfeeding” WeChat mini-programs and master the ability to teach parents how to use it. Each intervention group unit will formulate a corresponding implementation process based on the actual management situation of the unit. The supervision unit will set up a “Ning BX breastfeeding” WeChat mini-programs communication group to communicate difficulties and doubts encountered in the implementation process over time and provide help to some units encountering relatively difficult implementation.

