### Control group

The control group will be given routine management according to the existing management measures and policies of the unit, such as being provided with traditional education and the task of completing a breast milk paper diary. The control unit will not use the “Ning BX breastfeeding” WeChat mini-programs.

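### Guardians are asked for consent after unblinded NICU allocation, and the only consent taker named is the app's educators, so the arms can differ in which mothers are enrolled

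*Protocol article*

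**What the plan says.** All references are to the protocol article.

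- **Allocation and blinding (Randomization).** "Twelve units will be randomized into two groups (intervention and control groups) instead of patient randomization". The same section concedes that "the intervention cannot be completely blinded in this study".
- **Preparation (Pre intervention training).** Before the study, each intervention unit sets up an app "implementation team comprising at least one neonatologist and one neonatal nurse", whose members must be able to teach parents to use the app. No such team is described for control units.
- **Enrolment period (Sample size calculation).** Infants are recruited over one year in 12 NICUs.
- **Consent requirement (Inclusion and Exclusion criteria).** "The guardians of all preterm infants will provide informed consent". The exclusion list includes "No parental consent".
- **Consent taker (Intervention).** "The WeChat mini-programs educators will be responsible for obtaining informed consent from the guardians of premature infants". No other consent taker is named.
- **Control units (Control group).** "The control group will be given routine management according to the existing management measures and policies of the unit". This includes traditional education and a paper milk diary. The app is not used.
- **Adjustment (Statistical analysis; Discussion, limitations).** The covariates given as examples are gestational age, small for gestational age, gender and 5-minute Apgar score, plus NICU admissions and NICU MOM rate. The limitations paragraph adds birth weight and treatment level, and a multilevel model.

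**The concern.** Randomising units protects the comparison of units. It does not protect the comparison of infants when infants enter later, by consent, through staff who know the arm. The primary outcome is each infant's share of milk that is the mother's own, which depends directly on whether the mother pumps. In the app she logs each pumping session. It is plausible that a mother who does not mean to pump is less willing to agree when the person asking is there to teach that app. If the request, or the person making it, differs between arms, the consenting mothers can differ too.

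The article's Background says that socioeconomic, cultural and personal factors influence breastfeeding success. None of the named covariates measures a mother's intention or motivation, so neither the matching of NICUs nor the planned adjustment would remove such a difference. It would be read as an effect of the app.

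**Working it through.** **1. Does consent come after allocation?** No sentence says so outright, and the schedule of enrolment (Fig. 2) is not shown. It follows from three statements together: units are randomised, intervention units train their teams before the study, and infants are then recruited over a year. Staff approaching a guardian know their unit's arm.

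**2. Does consent decide who is analysed?** Yes. It is an inclusion criterion for all infants, and its absence is an exclusion criterion, in both arms.

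**3. Is the consent taker independent of arm?** The only role named is the app's educators. The term is not defined. The text ties app teaching to intervention units and says that control units do not use the app. No consent taker is named for control units, and no arm-independent recruiter is described.

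**4. Possible size.** The article gives no refusal rates, so these inputs are assumed. Let r be the refusal share in an arm and g the gap in MOM percentage between infants of consenting and refusing mothers.

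Mean of enrolled − mean of eligible = r × g

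Bias between arms = (r in intervention − r in control) × g, if g is the same in both arms

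| Refusal, intervention vs control | g = 10 | g = 20 | g = 30 |
|---|---|---|---|
| 5% vs 5% | 0 | 0 | 0 |
| 10% vs 5% | +0.5 | +1 | +1.5 |
| 20% vs 5% | +1.5 | +3 | +4.5 |
| 5% vs 10% | −0.5 | −1 | −1.5 |

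For example, 0.20 × 20 − 0.05 × 20 = 4 − 1 = 3 points. Against the 6-point difference in the sample size section, 1 point is 17% and 3 points is 50%. The last row shows that the sign reverses if refusal is higher in control units.

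**5. Effect on the test.** From the plan's own inputs (SD 30, intracluster correlation 0.005, 135 infants per NICU, 810 per arm):

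- Design effect = 1 + 134 × 0.005 = 1.67
- Standard error = √(2 × 30² × 1.67 / 810) = 1.93 points

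With no true effect, a two-sided 5% test (normal approximation) would be significant about 8% of the time under a 1-point bias and about 34% under a 3-point bias.

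The stated 90% power does not reproduce exactly: these inputs give 87.6% on the same approximation. That is a separate matter and does not bear on this point.

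**The case against.** The strongest reply is that the consent sentence stands in the Intervention section, beside app registration and information sharing, and may mean consent to use the app rather than to join the trial. Trial consent would then be the separate requirement for all infants. How it is obtained in control units is the kind of detail a condensed article leaves to the full protocol. This reading is possible. On it, however, recruitment is still unblinded and no arm-independent process is described, so the risk is reduced but not removed.

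Four stronger readings are tempting, and the document supports none of them:

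- *Educators exist only in intervention units.* This is a reasonable inference, but the role is undefined and never equated with the implementation team.
- *Control guardians are asked only for use of their data.* Nothing states what they are asked. Control mothers also keep a milk diary, on paper and as routine management, so the contrast may be smaller than it looks.
- *Selection acts in one arm only.* Consent is required, and refusal excludes, in both arms. The issue is possible differential selection.
- *The bias favours the intervention.* This is not derivable. Mothers with lactation difficulties might be the most eager for a consultation app, which could reverse the sign.

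It is also fair to say that the adjustment list is introduced by way of example and includes NICU-level variables. What stands is that nothing named measures maternal intention.

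**Conclusion.** The point holds as a design weakness that should be addressed. As written, the plan lets enrolment depend on a consent step taken with knowledge of the arm, through a role tied to one arm's intervention, with refusers excluded. The arms can therefore differ in maternal motivation, and the named covariates would not correct this.

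The document does not show that bias has occurred, nor its direction or size. The 1-to-3-point figure rests on an assumed 20-point gap and on assumed refusal of 10% to 20% against 5%. With equal refusal and an equal gap it is zero. The conclusion also rests on two inferences: that consent follows allocation, which the text supports strongly, and that the educators belong to the intervention units, which it supports less firmly.

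**What to change.** **For any infants still to be enrolled**

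- Use the same consent request in all 12 NICUs, taken by existing ward or database staff rather than app educators, for consecutive eligible admissions.
- Make acceptance of the app a separate, later step that does not affect enrolment.
- State that consented infants whose guardians decline or stop the app are analysed in their NICU's arm. The article does not say they would be dropped, so this settles an open point.

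**For infants already enrolled**

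The Trial status section puts the start in June 2020 and the end of the project in May 2021, and refers to completion in March 2021. Recruitment is therefore well advanced or finished, and the consent process may no longer be open to change. What remains is to:

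- state who took consent in control units and what guardians were asked;
- report eligible and consented counts by NICU;
- compare eligible with enrolled infants by arm, as far as the online database holds infants who were not enrolled.

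**Cost.** Revised consent wording and reassignment of the task to existing staff, plus a short descriptive table. Including app decliners dilutes the estimated effect slightly. The comparison by arm can reveal imbalance in recorded characteristics, but it cannot show that maternal motivation was balanced.

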**Fig. 3 Fig3:**
[figure not shown]
Function of instructions for the “Ning BX breastfeeding” WeChat mini-programs

### Part 1 Mother’s Daily

The mother’s daily lactation information, such as the number of pumps, volume of feeding by pumping, number of feeding sessions, and volume of feeding, is recorded. The mother can record the time, place, mode, and volume of each pump in detail, and a curve is constructed between the number and volume of pumps. By continuously uploading information from the mother, a breastfeeding evaluation can be automatically performed to assess information such as first lactation time, the start time of lactation phase II, and the start time of lactation, which are divided into three levels: good, average, and poor. This feature can record the entire process of a mother’s lactation, which is different from the traditional paper diary or recall recording of the pumped milk information. It can assess lactation information in a more timely and accurate manner and can provide professional guidance and intervention for mothers who have difficulty starting lactation in a timely manner.

### Part 2 Baby Feeding

Baby feeding is used to record the daily feeding information of premature infants discharged from the NICU after returning home. The mother can upload the time, volume, type (mother’s own milk, amino acid formula, ordinary formula), and daily weight of the infant. The program can evaluate whether the infant is fed adequately and whether the weight growth is within the normal range according to the amount and weight of the infant to guide the mothers of premature infants on whether professional outpatient consultation is needed. Because this study will focus on premature infants during hospitalization, this section is not currently available.

### Part 3 Growth Record

The growth record is used to interact with mothers of preterm infants admitted to the NICU. Doctors or nurses can upload photographs of babies in the NICU who are separated from their mothers and other infants to inform the mothers about the current situation and to promote earlier lactation by mothers. Additionally, this feature also has the function of communication. The mothers of premature infants can communicate with their assigned doctor, ask about the current diagnosis and treatment of the baby and feeding situation, assess the difficulties and challenges encountered in the process of breastfeeding, and obtain responses to questions from professional personnel.

### Part 4 Growth Curve

A growth curve is used to record the growth indicators of premature infants, such as weight, length, and head circumference, and carry out nutritional risk assessment and feeding guidance using this information. The mother can regularly upload the baby’s weight, length, and head circumference records, automatically generate the Fenton growth curve, and carry out nutrition risk assessment to determine whether the baby’s growth and development are normal. Additionally, the growth curve can provide feeding guidance or suggestions for the growth and development clinic according to the assessment results. This section is currently not available.

### Pre intervention training

Before the study, the supervision unit will be responsible for the training on the use of the “Ning BX breastfeeding” WeChat mini-programs and the development of a user guide. The intervention group unit will establish a “Ning BX breastfeeding” WeChat mini-programs implementation team comprising at least one neonatologist and one neonatal nurse. Each participant needs to be trained in the use of the “Ning BX breastfeeding” WeChat mini-programs and master the ability to teach parents how to use it. Each intervention group unit will formulate a corresponding implementation process based on the actual management situation of the unit. The supervision unit will set up a “Ning BX breastfeeding” WeChat mini-programs communication group to communicate difficulties and doubts encountered in the implementation process over time and provide help to some units encountering relatively difficult implementation.

### Quality control of implementation process

The supervision unit is responsible for the quality control, technical support, and experience transfer of the entire implementation process and is assigned by a dedicated person. The unit includes the following aspects: (1) the supervision unit regularly assigns professionals to the site to provide guidance and propose problems and solutions; (2) each participating unit surveys the user regarding his/her experience with the mini-programs, initially and during and after use if needed; (3) the “Ning BX breastfeeding” WeChat mini-programs data will be exported every month for data quality control, assessment of feedback problems, and provision of timely updates; and (4) a face-to-face session to assess and compare the doctor user and guardian user versions will be held to promote the best use of the WeChat mini-programs. ⑤If adverse events occur in the process of implementation, the participating units shall collecting and report to the supervision unit. Finally, the ethics committee make a decision, and the supervision unit shall inform the participating units of the results.

### Control group

The control group will be given routine management according to the existing management measures and policies of the unit, such as being provided with traditional education and the task of completing a breast milk paper diary. The control unit will not use the “Ning BX breastfeeding” WeChat mini-programs.

### Data collection

The data collection in this study will be performed according to the online database “NingBX neonatal homogeneity platform” (https://www.ningbx.com/) developed by a collaboration group in 2019. The basic data required for this study, such as the birth time, gestational age, weight, diagnosis and treatment process, complications, outcome, and other information, will all be obtained from the online database. The data related to breastfeeding will also be obtained from online databases, such as MOM at the time of feed initiation (hours), proportion of first-time MOM (%), duration of parenteral nutrition (days), time to total gastrointestinal feeding (days), total volume of breastfeeding per day, and total volume of breastfeeding during hospitalization. All the data in the online database will be input by professional personnel who are trained and qualified for entry. The database quality control personnel regularly control and feedback the data, and the database can modify and update the information in real time, as well as export the data in real time for data quality control and statistical analysis. Some of the database content is provided in Additional file 2.

### Data management

Nanjing Maternity and Child Health Care Hospital, as the supervision unit, will formulate the database entry guide and provide a detailed definition of each variable in the database to ensure the consistency of data entry. The data entry personnel shall be doctors or postgraduates with rich clinical experience in neonatology, and the chief physician of neonatology or personnel with a higher professional title shall be data quality control personnel. The supervision unit is responsible for the selection, training and assessment of the input, as well as for quality control personnel in the cooperation group. Only those who regularly participate in the training and pass the assessment can participate in the data entry work and become database entry personnel. Additionally, the supervision unit will be responsible for regular training, mid-term assessment and year-end summary of data entry throughout the entire research period. The supervision unit will hold an online meeting for the quality controller and recorder every month to discuss the problems encountered with the recent input and quality control data, rectification plan, and experience sharing. The professional personnel in charge of the database management of the supervision unit will conduct unified quality control for all data, generate a summary, and provide feedback on the opinions to all participating units in a timely manner. Statistical experts will analyse the data every 3 months, summarize the statistical results, and recheck and update the ambiguous results. In addition, the supervision unit as the coordination centre is responsible for analysing and publishing the data in an anonymized form. The data monitoring committee consists of the data quality control personnel of the coordination centre and chief investigators of 12 participating NICUs, and it will be responsible for monitoring the conduct of the study to ensure compliance with the study protocol. The committee is also responsible for other aspects, including providing study materials, checking and analysing data, and publishing study reports (if there are any changes to the protocol, the new study report through email and WeChat mini-programs inform 12 participating NICUs). The ethics committee, which is independent of the sponsor and investigators, will audit the conduct of the study annually.

### Data association

The doctor and guardian versions of the data in the WeChat mini-programs can be shared and stored in an online database. The online database has a special data export function for the “Ning BX breastfeeding” WeChat mini-programs. The three functions form a closed loop, which can realize the timely export and sharing of the data (Fig. 3).

### Statistical analysis

Statistical analysis will be performed by statisticians; continuous variables will be presented as the means and standard deviations, and categorical variables will be presented as numbers and proportions. Adjusted chi-square analysis will be performed to compare the primary outcome indicators of the intervention and control groups, and the cluster effect will be considered. The two-level stratified logistic regression model will be used to compare the main outcome indicators between the two groups.

Superiority test will be used if necessary. The results will be adjusted based on an evaluation of neonatal characteristics (such as gestational age, small for gestational age, gender, and 5-min Apgar score) and NICU characteristics (number of preterm infants admitted and rate of MOM feeding). All statistical tests will be two-tailed, and *P* < 0.05 will be considered significant.

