### Sample size calculation

The proposed sample size is based on the primary outcome of the proportion of MOM feeding. According to the baseline data reported (unpublished data) by each unit in 2019, the average proportion of MOM feeding was 42.46%. We expect the proportion of MOM feeding of premature infants during NICU hospitalization to increase by at least 15% in the intervention group compared with that in the control group. We will achieve 90% power to detect a difference between the group means of at least 6, and the standard deviation of subjects is 30.00, assuming the intracluster correlation coefficient is 0.005 [21, 22]. We estimate a total sample size of 1620 (810 in the intervention group and an average of 135 in each group). Considering a 10% drop-out rate following enrolment in the study, we will enrol 900 premature infants in the intervention and control groups. To achieve this sample size, we will conduct a 1-year study in 12 NICUs.

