### Outcome and definitions

The primary outcome is the proportion of MOM feeding of premature infants during NICU hospitalization.

The secondary outcomes are as follows (Table 1): (1) MOM at feeding initiation (hours) and proportion of first-time use of MOM (%); (2) duration of parenteral nutrition (days); (3) time to total gastrointestinal feeding (days); (4) hospitalization time and cost; and (5) incidence of complications, such as NEC, BPD, LOS, and ROP.

**Table 1 Tab1:** Outcome and definitions

Categories		Source of data	Implementation process control	Definitions
**Primary outcomes**	Proportion of MOM feeding of premature infants during NICU hospitalization [23]	Online database	Continuous data entry of each unit regular data export for statistics	Calculated to determine the relative amount of MOM and total milk (human milk+formula, TM) taken by each infant during NICU hospitalization [mLsMOM/mLsTM]*100
**Secondary outcomes**	Time (h) of first mother’s own milk and proportion of mother’s own milk (%)	Online database	Continuous data entry of each unit regular data export for statistics	Time after birth to the first MOM and proportion of the first MOM to the total milk
	Duration of parenteral nutrition (d)	Online database		Duration of total parenteral nutrition required for complete fasting in preterm infants
	Time to full enteral gastrointestinal feeding (d)	Online database		Full enteral gastrointestinal feeding is defined as no longer in need of parenteral nutrition or fluid
	Hospitalization time and cost	Online database		Hospitalization time is the time in the NICU, and hospitalization cost is the total cost during the hospital stay
	Incidence of complications (NEC, BPD, LOS, and ROP )[24]	Online database		Incidence of common complications in preterm infants, such as necrotizing enterocolitis (NEC), bronchopulmonary dysplasia (BPD), late-onset sepsis (LOS), and retinopathy of prematurity (ROP)

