## Discussion

This is the first cluster randomized controlled trial in China in which WeChat mini-programs will be used to improve MOM feeding during the hospitalization of premature infants. The goal of this study is to increase the proportion of NICU premature infants receiving MOM during hospitalization through the intervention of WeChat mini-programs. If the implementation of the program is successful, it can be promoted in other NICUs.

Breastfeeding for mothers of NICU preterm infants is associated with more challenges than that for mothers of full-term infants. Foreign studies have shown that the rate of MOM feeding of premature infants in the NICU is 76% [25]. However, a multicentre study in China revealed that the rate of exclusive MOM feeding of premature infants during hospitalization was only 20% [26]. Such a large gap is related not only to the management policy of the NICU in China but also to the anxiety and negative emotions of mothers and their families of premature infants and, more importantly, to the lack of effective lactation counselling interventions. WeChat mini-programs can help mothers of preterm infants better participate in the medical process, enhance the emotional communication between mothers and infants, and help prolong breastfeeding. During the novel coronavirus (COVID-19) epidemic period, the communication function of WeChat mini-programs played a significant role. Family members and society should be encouraged to provide more support to pregnant women to improve their confidence in breastfeeding. The purpose of this study is to evaluate the effect of WeChat mini-programs lactation consultation on increasing the proportion of MOM feeding in premature infants in the NICU. We assume that the proportion of MOM feeding in the intervention group will be much higher than that in the control group, and this project can be carried out for a long time.

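### The primary outcome is defined and sized as a mean percentage per infant, but the tests named for it are a chi-square test and a logistic model, with no cut-off given

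*Protocol article*

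**What the plan says.** **Outcome (Outcome and definitions, Table 1).** The primary outcome is "Calculated to determine the relative amount of MOM and total milk (human milk+formula, TM) taken by each infant during NICU hospitalization [mLsMOM/mLsTM]*100". Each infant contributes one number between 0 and 100. No threshold is given here or elsewhere in the article.

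**Sizing (Sample size calculation).** The trial is powered at 90% to "detect a difference between the group means of at least 6, and the standard deviation of subjects is 30.00", with an ICC of 0.005, 810 infants per arm and 135 per NICU.

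**Analysis (Statistical analysis).** Two methods are assigned to the primary outcome: "Adjusted chi-square analysis will be performed to compare the primary outcome indicators of the intervention and control groups", with clustering taken into account, and "The two-level stratified logistic regression model will be used to compare the main outcome indicators between the two groups". Means and SDs appear in this section only as descriptive summaries. The limitations paragraph of the Discussion mentions multilevel models for the primary outcome but gives no type.

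**Goal (Discussion).** One sentence reads "The goal of this study is to increase the proportion of NICU premature infants receiving MOM during hospitalization", which counts infants rather than measuring a volume share.

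**The concern.** The definition and the sample size describe a continuous outcome, while the named tests belong to categorical data. To run the chi-square test, the analyst must first turn each infant's percentage into a category, and the protocol does not say where to cut. A standard logistic model needs the same step and returns an odds ratio, not a difference in percentage points.

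Three things are at stake. The 6-point difference in means would not be estimated by any named primary method. The trial would have less power than the calculation on which it was sized. The cut-off, and with it the question answered, would be left to whoever runs the analysis.

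**Working it through.** **Inputs.** From Sample size calculation: difference 6, SD 30, ICC 0.005, 810 per arm, 135 per NICU, baseline mean 42.46. From Study design: 6 NICUs per arm, matched in pairs. From Statistical analysis: two-sided test at 0.05.

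**Step 1: which scale was the trial sized on?**

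- Per arm without clustering: 2 × (1.960 + 1.282)² × 30² / 6² = 525.4, so 526.
- Design effect: 1 + (135 − 1) × 0.005 = 1.67.
- Per arm with clustering: 526 × 1.67 = 878.4, so 879.

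This does not reproduce the stated 810 (an ICC of 0.004 would give 526 × 1.536 = 808). That gap is a separate matter. What counts here is that the calculation uses a difference in means and an SD, so the sized target is a mean difference.

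**Step 2: power for the comparison of means at 810 per arm.**

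- Standard error: 30 × √(2 × 1.67 / 810) = 1.926 points.
- Non-centrality: 6 / 1.926 = 3.11.
- Power: 87.6% (normal) or 80.1% (t, 10 df for 12 NICUs).

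**Step 3: power if the percentage is dichotomised.** Assume approximate normality with means 42.46 and 48.46 and SD 30, and carry the ICC of 0.005 over to the binary scale. For cut-off c, the share above it is p = 1 − Φ((c − mean)/30) in each arm. The non-centrality is (p₂ − p₁) / √{[p₁(1 − p₁) + p₂(1 − p₂)] × 1.67 / 810}.

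| Cut-off | p₁ | p₂ | Difference | Non-centrality | Power, normal | Power, t (10 df) |
|---|---|---|---|---|---|---|
| 20 | 0.773 | 0.829 | 0.056 | 2.17 | 58% | 50% |
| 30 | 0.661 | 0.731 | 0.070 | 2.37 | 66% | 57% |
| 42.46 | 0.500 | 0.579 | 0.079 | 2.48 | 70% | 61% |
| 50 | 0.401 | 0.480 | 0.079 | 2.48 | 70% | 61% |
| 60 | 0.279 | 0.350 | 0.071 | 2.38 | 66% | 58% |

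**Step 4: loss of efficiency.** The squared ratio of non-centralities gives the share retained. At the control mean it is (2.48 / 3.11)² = 0.64, a loss of about a third. At a cut-off of 20 it is (2.17 / 3.11)² = 0.49, a loss of about half.

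**The case against.** **Logistic need not mean binary.** A logit model can be fitted to a 0–1 share as a fractional response. This stands: it would be wrong to say that any logistic model needs a yes/no outcome. But the article does not state that formulation, it still would not report a mean difference directly, and it does not help the chi-square test.

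**The SAP may settle it.** That would answer an omission. Here the protocol names methods, and an SAP that followed it would inherit the mismatch.

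**The methods suit the complications.** They do suit NEC, BPD, LOS and ROP, but the section attaches them to the primary and main outcome indicators.

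**Stronger readings that the documents do not support.**

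- A reader might take 42.46% as the share of infants with an event, compare it with 48.46%, and find a much larger loss of power than shown above. But 42.46 is reported as an average proportion of MOM feeding, and nothing says that a headcount would rise by the same 6 points.
- A reader might infer that dichotomising throws away most of the information. Step 4 shows about a third for a split near the centre.
- A reader might fear that each mL of milk will be entered as an independent trial. Nothing in the article suggests this.
- A reader might object that two primary tests are left unranked. They can be read as a crude comparison followed by an adjusted model, and the order is ordinary SAP content.
- A reader might see a second estimand in the Discussion goal. The same section later states the purpose in terms that match Table 1, so this is better seen as loose wording to align.

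**Conclusion.** The point holds. The outcome definition and the sample size describe a mean percentage, and neither method named for the primary outcome, as stated, tests a difference in means. The chi-square test cannot be run at all without a cut-off that the article does not give.

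If the outcome were dichotomised at a cut-off between 20 and 60, power would fall from about 88% to 58–70% (normal), or from about 80% to 50–61% (t, 10 df). These figures are illustrative. They rest on a shift of 6 applied to a roughly normal outcome and on the same ICC for the binary version. The normal curve is only rough here: 0 lies 42.46 / 30 = 1.42 SD below the mean, so it would put about 8% of infants below zero. The article also speaks of an increase of at least 15% without saying whether this is relative or absolute. The figures use the 6 points on which it sized the trial. The mismatch itself depends on none of these assumptions.

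**What to change.** Replace the two tests for the primary outcome with one cluster-adjusted comparison of the infant-level MOM percentage that respects the six matched pairs. Either of these would do:

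- a linear mixed model with a treatment effect, a NICU random intercept and a pair term, using small-sample degrees of freedom; or
- a paired comparison of NICU mean percentages.

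Report the mean difference in percentage points with a 95% CI. Use a within-pair permutation test or a fractional-response model as a sensitivity analysis. Keep chi-square and logistic methods for the binary secondary outcomes (NEC, BPD, LOS, ROP), and reword the Discussion goal to match Table 1.

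This changes wording only and needs no new data or infants. The team should know one consequence: a paired analysis of six pairs has 5 df. At the non-centrality of 3.11 this gives about 70% power before any gain from matching, so the choice between the two forms should be fixed before the groups are compared.
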